### Study area

Yogyakarta district is a city in Indonesia that experiences a significant
prevalence of HIV cases among the deaf population. The participants targeted for
this study will be individuals associated with the Gerkatin NGO in Yogyakarta,
Indonesia.

### Study design

This study will employ a quasi-experimental, non-randomized controlled trial
design with single blinding applied to participants. The control group will
receive standard therapy, while the intervention group will receive the mobile
health program. A parallel assignment approach will be used, reflecting the
structure of health services research. This study corresponds to a Phase
2–3 trial, aiming to evaluate both the feasibility and preliminary
effectiveness of the intervention. One or two (experimental group) receives the
Mobile health KaPi Program intervention under test and the other (comparison
group or control) receives the standard e book/leaflet. Then follow up on the
two or more groups to see if there are any differences in the results. The
results of the study and subsequent analysis are used to assess the
effectiveness of the intervention mobile health application. Quasi-experimental
are the most rigorous way to determine if there is a causal link between
interventions and outcomes ( Polit and Beck, 2017).  Figure 1 provides an
overview of the study design. The choice of this experimental design is grounded
in its robustness and efficacy ( Creswell, 2016).

**Figure 1. f1:**
[figure not shown]
Summarized the study design.

### Inclusion and exclusion criteria participants

Inclusion and exclusion criteria are clearly defined to ensure that the study
population is representative of the target demographic. The study consisted of
deaf Indonesian nationals 1. Age 18 to 65 years. 2. All gender (Male, Female,
and other) 3. Sexually active 4. Has access to a smart phone. This study will
exclude those who are deaf and 1. pregnant, 2. already diagnosed with HIV/AIDS,
3. illiterate 4. can’t speak Indonesian sign language. This careful
selection process helps to control for confounding variables that could affect
the outcomes, such as pre-existing health conditions or communication barriers (
Creswell, 2016; Hart et al., 2023). The significance of
well-defined inclusion criteria in enhancing the internal validity of health
research ( Bodicoat et al., 2021; Patino & Ferreira, 2018).

### Recruitment

To assess eligibility, the researcher will initiate contact with all regional
leaders of Gerkatin NGOs within the target district, facilitated through
coordination with the head of Gerkatin in the Yogyakarta area. This process will
be accompanied by a formal data collection permit issued by the
researcher’s affiliated university. The letter will be forwarded to the
regional Gerkatin head, who will then distribute it to local branch leaders to
support coordinated recruitment.

The recruitment strategy will apply multiple approaches commonly used to enhance
participation in research, such as early notification to Gerkatin leadership,
offering involvement opportunities, on-site visits to Gerkatin representatives,
outreach via phone and digital communication, and allowing potential
participants to consult with research staff regarding study participation.
Dedicated research personnel will supervise and document the recruitment
process.

Once permission is obtained, the Gerkatin head or a designated representative
will contact eligible individuals via telephone to assess inclusion criteria and
confirm their willingness to participate. Eligible participants will be provided
with detailed information and consent forms, including explanations in
Indonesian Sign Language, and asked to sign written consent forms.

To support participant retention throughout the three-month study period, a
dedicated WhatsApp group (WAG) will be created for enrolled participants. This
group will serve as a monitored communication platform for sending reminders,
providing support, and addressing questions related to the intervention and
follow-up activities. Periodic check-ins and app-based notifications will also
be used to promote sustained engagement. Participants will be reminded of their
right to withdraw from the study at any time without penalty. All study
procedures and timelines will be clearly explained in the Respondent Information
and Consent Forms.

To address potential technological barriers, the study will ensure that all
participants have access to a smartphone compatible with the KaPi mobile
application. For participants without a suitable device, the research team will
collaborate with local Gerkatin branches to provide access to shared devices or
temporary loaner phones during the study period. In addition, brief orientation
sessions will be conducted in Indonesian Sign Language to improve digital
literacy and familiarize users with app features. If participants experience
limited or unstable internet connectivity, the mobile app is designed to support
offline functionality, allowing them to access core content without continuous
internet access. These measures aim to minimize dropout due to technical
challenges and ensure inclusive participation.

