### Deaf person is risk population for health ethics and consent

The trial protocol of this study was approved by head of ethics review committe
[name], S.Kep., Ns., M.Kep., Sp.Kep.MB., PhD.NS on 05 November
2023, by Health Research Ethics Committee STIKES Bethesda Yakkum, Indonesia have
granted ethical approval No.036/KEPK.02.01/V/2023 and Trial registration: Sri
Lanka Clinical Trials Registry (SLCTR) with number SLCTR/2024/039 on 25 November
2024, https://slctr.lk/trials/slctr-2024-039.

All participants will be provided with detailed study information delivered in
Indonesian Sign Language to ensure accessibility for deaf individuals. To
confirm their understanding, comprehension questions and interactive elements
will be used before obtaining informed consent. Informed consent will be
obtained through a combination of video-recorded agreements using sign language
and a signed written consent form as formal documentation.

Participation is completely voluntary with no coercion. Participants have the
right to withdraw at any time without penalty, and this will be clearly
communicated during the consent process.

Data collected via the mobile application will be securely stored on encrypted
servers accessible only to authorized research staff. Participant anonymity will
be maintained by using unique codes, and no identifiable information will be
published. Procedures for protecting data privacy and for
withdrawal—including deletion of data upon participant request—are
clearly detailed in the Respondent Information and Consent Forms.

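### The shared WhatsApp group makes enrolled participants visible to each other, and the plan does not reconcile this with the anonymity it states

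*Protocol article*

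**What the plan says.** Under Recruitment, the protocol article states that a "dedicated WhatsApp group (WAG) will be created for enrolled participants" and that this "group will serve as a monitored communication platform for sending reminders". It adds two further uses: giving support, and dealing with questions about the intervention and the follow-up. Periodic check-ins and notifications through the app are planned as well.

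The inclusion and exclusion criteria require participants to be "3. Sexually active 4. Has access to a smart phone" owners or users, and they "exclude those who are deaf and 1. pregnant, 2. already diagnosed with HIV/AIDS", along with people who are illiterate or do not use Indonesian Sign Language. The Study area section draws participants from a single NGO in Yogyakarta.

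The ethics and consent section has a paragraph on data protection. It opens with "Data collected via the mobile application will be securely stored on encrypted" servers that only authorised research staff can reach. It then says that anonymity will "be maintained by using unique codes, and no identifiable information will be" published. That paragraph does not mention the WhatsApp group. Nor does the article say how members appear to each other, whether joining is optional, or whether there is one group or one per arm.

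**The concern.** A group chat is a channel among participants, not only between staff and participant. In most trials, being known to other participants matters little. Here enrolment itself carries information, because the entry criteria concern sexual activity and HIV diagnosis. The questions expected in the group concern a programme on HIV prevention and psychological distress. Participants come from one NGO network, so some may already know each other. If the plan is followed as written, participants are exposed to one another in a way that the stated anonymity measures do not address. What is at stake is confidentiality, not the validity of an estimate.

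**Working it through.** The article gives no figure on this point, so the check sets the sections side by side.

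1. **Who is in the group.** Recruitment: enrolled participants. Membership therefore marks a person as enrolled.
2. **What enrolment implies.** Inclusion and exclusion criteria: sexually active, and not "already diagnosed with HIV/AIDS". Anyone who knows the criteria and sees a member can infer both.
3. **What is discussed there.** Recruitment sends questions about the intervention to the group. The description of the KaPi programme lists HIV prevention, coping with distress and self-efficacy. A question posted there can therefore reveal a personal concern on these topics.
4. **Whether the stated safeguards reach the group.**

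| Safeguard in the ethics section | What it covers | Does the group breach it? | Does it protect members from each other? |
|---|---|---|---|
| Encrypted servers with staff-only access | Data collected through the app | No | No; group messages are not app data |
| Unique codes | Identity in the study records | No | No; codes are not said to apply in the chat |
| No identifiable information published | Reports and publications | No | No; the chat is not a publication |

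None of the three is broken, and none reaches the exposure.

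5. **How many people could see each participant.** The Sample size section targets 40 per group, 80 in total.
   - One group for everyone: 80 − 1 = 79 others at most.
   - One group per arm: 40 − 1 = 39 others at most.

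   Splitting by arm, which one might do to limit contamination, reduces the number but leaves the exposure in place.
6. **Whether retention depends on the group.** Recruitment already provides check-ins and app notifications, so reminders do not need a channel in which participants see each other.

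**The case against.** The strongest reply has four parts.

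- **Visibility is inferred.** The article does not say what members can see, whether joining is required, or how many groups there are. This is right, and the point is therefore stated as following from ordinary use of such a group. Still, a channel in which participants' questions are handled is ordinarily visible to its members, and no setting that would prevent this is described.
- **The consent forms are not shown.** They are said to explain all study procedures and to detail data privacy, so they may disclose the group. This stands as a limit on what can be said about what participants are told. Disclosure would inform participants, but it would not make them unknown to each other.
- **The NGO already knows.** Its head or a representative telephones people to check eligibility, and local branches help with devices, so participation is not secret in the network. This is true, but it does not make exposure to every co-participant necessary.
- **Peer support has value.** This stands, and it is the real cost of the change.

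A reader might infer more than the document supports:

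- **A direct contradiction of the anonymity promise.** The promise sits in a paragraph on app data and works through coding and non-publication. The group breaches neither.
- **That absence from the group, or leaving it, reveals a failed criterion.** Participation is voluntary and unpaid, withdrawal is free at any time, and several criteria (age, smartphone, literacy, sign language) have nothing to do with HIV or pregnancy.
- **That the group biases self-report or drives dropout.** Nothing says that questionnaire answers are visible there, and the document gives no evidence for either effect.
- **That all three primary outcomes are stigma-sensitive.** The knowledge part of the HIV testing questionnaire is scored on correct answers.

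**Conclusion.** The point holds as a gap between two sections. Recruitment sets up a shared channel that, in ordinary use, identifies enrolled participants and their questions to each other. The anonymity stated in the ethics section does not extend to that exposure. It rests on two assumptions: that the group works as WhatsApp groups ordinarily do, and that no arrangement in the unseen consent forms hides members from one another. Its reach is the upper bound of 79 or 39 co-participants given above. It is a confidentiality matter with no consequence for power, the analysis model or any reported figure, and it is separate from questions of blinding or contamination. It merits a change because the exposure is avoidable at little cost.

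**What to change.** In Recruitment, replace the group with one-to-one messages, or with a broadcast list sent from a study number in which recipients cannot see each other. Say that questions are answered privately, and apply the same arrangement in both arms. In the ethics and consent section, add a sentence extending the anonymity statement to contact during the study, so that it covers exposure to other participants as well as stored and published data. Check that the consent forms agree.

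The reminders can stay the same. The cost is some loss of peer support and slightly more individual replies for staff.

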### Sample size

The sample size was determined using the software Based on an a priori power
analysis (G*Power 3.1) ( Faul et al., 2007). An *F*-test (ANOVA: repeated
measures, within-between interaction) was selected as the statistical test,
assuming two groups (intervention and control). The analysis used a conventional
alpha level (α) of 0.05, a statistical power (1 - β) of 0.95, and
a small to medium effect size (f = 0.20), in line with guideline from ( Chow et al., 2002). Based on the
parameters, the minimum required sample size was calculated to be 66
participants (33 per group).

 To account for potential attrition, a 20% dropout rate was anticipated, as
supported by previous studies ( In et al., 2020; Suresh & Chandrashekara, 2012). The adjustment led to an additional 7 participants per group,
resulting in a final target sample size of 40 participants per group, or total
of 80 deaf participants for this study. The final analysis will be conducted
using Generalized Estimating Equations (GEE) to account for the correlated
nature of repeated measures over time and provide robust estimates of
intervention effects.

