### Statistical analysis

Demographic characteristics and predictor variables were summarized as
frequencies (n) and percentages (%) for categorical data, and means with
standard deviations for continuous data. Descriptive statistics, including
percentage and frequency distributions, are presented using tables and charts.
Chi-square tests and independent t-tests (or ANOVA where appropriate) were used
to compare socioeconomic and baseline characteristics between the two study
groups.

For inferential analysis, the association between each independent variable and
the outcome variable was initially examined using binary logistic regression.
The primary outcomes—psychological distress (K10), HIV prevention
knowledge and practices (KAP VCT), and communication self-efficacy
(CSE)—were analyzed using Generalized Estimating Equations (GEE) to
account for repeated measures and within-subject correlations over time. The GEE
model included main effects of group and time, as well as their interaction term
(group × time), to evaluate differential changes between intervention and
control groups across three measurement points (baseline, post-intervention, and
4-week follow-up). Adjusted odds ratios with 95% confidence intervals are
reported.

Missing data will be handled under the missing at random (MAR) assumption
inherent in GEE, and sensitivity analyses will be conducted to assess the
robustness of findings.

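### The dropout allowance is too small: at the stated 20% loss, 40 per group leaves 32, one below the stated minimum of 33

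*Protocol article*

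**What the plan says.** The Sample size section of the protocol article bases the calculation on a repeated-measures ANOVA F-test of the within-between interaction with two groups. It uses alpha 0.05, "a statistical power (1 - β) of 0.95" and Cohen's f of 0.20, and arrives at a minimum of 66 participants, 33 per group.

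It then turns to attrition: "To account for potential attrition, a 20% dropout rate was anticipated, as" (the sentence goes on to cite two sources). The size of the allowance comes next: "The adjustment led to an additional 7 participants per group". That brings planned enrolment to 40 in each arm, 80 overall.

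The Methods part of the Abstract repeats 40 per group and 80 in total. Nowhere does the article give a different dropout rate or a further allowance. It does not write out the formula that led from 33 to 40.

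**The concern.** An attrition allowance has one purpose: the number still in the trial after the expected losses should be no smaller than the number the power calculation requires. A dropout rate applies to the people enrolled, so the required number has to be divided by one minus the rate. An increase of 7 on a base of 33 looks instead like 20% of 33, rounded up.

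If so, the trial falls below its own minimum at its own expected dropout rate, and the planned 95% power is not quite secured. A reader would also wrongly take the trial to tolerate a 20% loss.

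**Working it through.** **Inputs from the article**

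- Sample size section: two equal groups, alpha 0.05, power 0.95, f = 0.20, minimum 66 (33 per group), dropout 20%, 7 added per group, target 40 per group (80).
- Statistical analysis section: three measurement points.

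**Inputs assumed**

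- Correlation between repeated measures ρ = 0.5 and nonsphericity correction ε = 1. The article states neither.

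**Step 1: reproduce the 66.** For k = 2 groups, m = 3 measurements and ε = 1, the test uses a noncentral F distribution with

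- λ = f² × N × m / (1 − ρ)
- df1 = (k − 1)(m − 1) = 2
- df2 = (N − k)(m − 1)

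| Total N | λ | df2 | Power |
|---|---|---|---|
| 66 | 0.04 × 66 × 3 / 0.5 = 15.84 | 128 | 0.9504 |
| 64 | 0.04 × 64 × 3 / 0.5 = 15.36 | 124 | 0.9439 |

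With equal groups, 66 is the smallest total that reaches 0.95, so the plan's figure is reproduced. It is sensitive to the assumed correlation: with m = 3 and power 0.95, the required total is 92 at ρ = 0.3, 66 at ρ = 0.5 and 42 at ρ = 0.7.

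**Step 2: reproduce the 40.**

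- 33 × (1 + 0.20) = 39.6, rounded up to 40. This matches.
- 33 / (1 − 0.20) = 41.25, rounded up to 42. This does not match, and 41.25 cannot round to 40.

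**Step 3: how many remain after a 20% loss?**

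| Enrolled per group | Remaining per group | At least 33? |
|---|---|---|
| 40 | 40 × 0.80 = 32 | No |
| 41 | 41 × 0.80 = 32.8 | No |
| 42 | 42 × 0.80 = 33.6 | Yes |

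At 40 per group the total remaining is 64, two below the minimum of 66. Inflating the total gives 66 / 0.80 = 82.5, so 83, which equal groups turn into 84.

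**Step 4: what dropout does 40 per group cover?** 1 − 33/40 = 7/40 = 17.5%.

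**Step 5: cost in power.** 0.9504 − 0.9439 = 0.0065, about 0.65 percentage points, under the assumed ρ and ε and counting completers only.

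Steps 3 and 4 use only printed figures and do not depend on ρ, on ε or on which formula the authors applied.

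**The case against.** The arithmetic is hard to dispute. The case on the other side concerns its weight.

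- **The loss is trivial.** About 0.65 points from a 95% target changes no reading of the trial. The unstated correlation matters far more, since it moves the required total between 42 and 92 over a plausible range. This stands and limits the importance of the point. It does not make the printed figures agree.
- **Dropping out is not the same as contributing nothing.** The planned analysis is GEE over three time points, so someone lost after the post-intervention visit still supplies two of the three measurements. The figure of 32 therefore counts completers, and 0.944 is a complete-case ANOVA figure that is probably somewhat pessimistic. This also stands. But the article sized the trial for the ANOVA and then adjusted it explicitly for attrition; it does not argue that partial data make up the difference.
- **The multiplication by 1.2 is inferred.** True: the article says only that 7 were added. The inference is strong, but the finding does not need it, because 33, 20% and 40 are inconsistent whatever the route.
- **The power figures are not the plan's own.** Correct: they rest on ρ = 0.5 and ε = 1. These values reproduce the 66, and that is the only support for them.

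**Conclusion.** The point holds. At the article's own 20% dropout, 40 per group leaves 32, one per group and two in total below its own minimum. The target tolerates 17.5% dropout, and a true 20% allowance would need 42 per group (84 in total).

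The headcount shortfall is certain from the printed numbers. Because 66 is the plan's own minimum for 0.95, 64 completers fall short of that power whatever correlation was used. The size of the shortfall, 0.944 against 0.950, depends on the assumed ρ = 0.5 and ε = 1 and on counting completers only. It is a small error that should be corrected because the sample-size justification relies on it; it does not threaten the trial.

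**What to change.** Keep 40 per group and correct the attrition sentence in the Sample size section in one of two ways:

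- state that 40 per group allows for 17.5% dropout while keeping 33 per group; or
- keep the 20% rate and state that 32 per group would then remain, with power of about 94%, naming the assumed correlation of 0.5 and sphericity (or whatever values were actually entered in the software).

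Either costs one sentence and leaves enrolment, design and analysis unchanged. If the sponsor does want 33 per group to remain after a 20% loss, the target becomes 42 per group, four more participants in total, and the Abstract must change with it. Given the size of the effect, that is not necessary once the sentence is right.

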### Outcome MHealth KaPi Program

Increase in physical and psychological capability of HIV voluntary counseling and
testing.

### Tools for collecting information in research

**Ebook Mental Health and HIV/AIDS**

The mental health and HIV/AIDS ebook contains general material related to mental
health, psychological disorders, coping efficacy, and HIV/AIDS. The material in
pdf can be accessed at https://doi.org/10.5281/zenodo.14784036 ( [name], 2025a) *, * Data are
available under the terms of the Creative
Commons Zero “No rights reserved” data waiver (CC0
1.0 Public domain dedication).

**Mobile Health KaPi Program**

The KaPi mobile health program consists of 11 structured sessions, each lasting
approximately 12 minutes. These sessions cover topics such as HIV prevention
strategies, coping mechanisms for psychological distress, and self-efficacy
improvement, all delivered through Indonesian sign language videos within the
app. The program application can download at playstore with link https://play.google.com/store/apps/details?id=com.project.kapi.
for the table this program can acces at https://doi.org/10.5281/zenodo.14784226 ( [name], 2025b), Data are available under the terms of the
Creative
Commons Zero “No rights reserved” data waiver (CC0
1.0 Public domain dedication).

